### Interventions

Participants randomly allocated to the control group at the single site will participate in ongoing conventional care, aimed at managing their cardiovascular health as directed by their family physician, ideally in consultation with their cardiologist. The control group will be advised to seek the advice of their family physician and cardiologist but will receive no additional intervention as a result of participation in the study.

Participants in both the CHOICE and CHOICE-*plus *groups will take part in a three-month patient-centred modular secondary prevention program. The CHOICE-*plus *group will also be offered additional face-to-face reinforcement at 12 and additional telephone reinforcement at six, 18 and 30 months.

As described elsewhere, the CHOICE intervention includes a one-hour initial consultation and follow-up phone calls over three months [20]. The program is designed to have an individualised, structured, case-management approach and is overseen by treating physicians. The development and implementation of the CHOICE program can be divided into four stages (figure 2). Stage one involves the development of modules and tailoring of leaflets to access recommended local services [21]. Stage two is a face-to-face risk factor assessment, lasting approximately one hour in which the patient is assisted to generate a list of their own relevant risk factors. In stage three, patients make guided choices about which risk factors they will address, participate in realistic goal-setting informed by national targets (table 1) [9] and then select management option(s) for lowering risk. The relevant patient information leaflets, described in Stage 1, support these choices. All CHOICE patients participate in the core module for lowering cholesterol as well as up to two choice modules from blood pressure (BP)-lowering, smoking cessation, increased physical activity and nutrition. Patients will have the option to add additional modules on completion of the three-month program. Additional module information will be given over the telephone and written information will be mailed to the patient. Stage four, is telephone follow-up, consisting of approximately four calls of around 10 minutes duration over a three-month period, during which each patient's risk factor(s) goals and strategies are re-evaluated and mutually changed if necessary. CHOICE-*plus *patients will receive additional telephone follow-up over 3 years as previously outlined (figure 1).

**Table 1 T1:** Risk factor targets

**Risk factor**	**National Heart Foundation of Australia targets **[9]
Smoking	Complete cessation
Nutrition	Establish and maintain healthy eating
Alcohol	Low risk alcohol consumption
Physical activity	30 minutes of moderate activity on most days of the week
Healthy weight	Waist measurement
	Male ≤ 94 cm Female ≤ 80 cm
	BMI 18.5–24.9 kg/m^2^
Lipids	LDL < 2.0 mmol/l
	HDL > 1.0 mmol/l
	Triglycerides < 1.5 mmol/l
Blood pressure	Adults ≥ 65 (unless they have diabetes and/or renal insufficiency and/or proteinuria ≥ 0.25 g/day) <140/90 mmHg
	Adults <65 years; adults with diabetes and/or renal insufficiency and/or proteinuria 0.25–1.0 g/day <130/80 mmHg
	Adults with proteinuria >1 g/day <125/75 mmHg
Diabetes	Identify those with previously undiagnosed type 2 diabetes. In those with diabetes maintain HbA1C ≤ 7.0%

**Figure 2 F2:**
[figure not shown]
Model of CHOICE (Choice of Health Options In prevention of Cardiovascular Events) program after acute coronary syndrome (ACS).

### Outcome measures

The primary outcomes are TC, systolic blood pressure (SBP), smoking rates and physical activity levels at 12 and 36 months (Table 2). Secondary outcomes include readmission rates, all-cause mortality, cardiac mortality, number of cardiac risk factors, waist circumference and process measures to assess barriers to implementation and fidelity to the intervention components (Table 2).

**Table 2 T2:** Trial end points

**Primary**
TC (fasting blood sample)
SBP (resting digital reading) [27,28]
Smoking rates (self report confirmed with carbon monoxide meter) [29-31]
Physical activity (Active Australia Questionnaire validated by accelerometry) [24,26]
**Secondary**
Readmission rates (hospital records)
All-cause mortality (hospital records)
Cardiac mortality (hospital records)
Waist circumference (tape measurement) [32]
Number of modifiable risk factors (sum)
Process evaluation measures (including recruitment, withdrawal, barriers to participation, number and length of interventions delivered)
**Tertiary**
Diet (achievement of heart foundation target) [9]
Quality of life (SF12) [33]
Depression (Depression scale-short form) [34]
Angina status (Canadian Cardiovascular Society class) [35]
Modifiable risk factor knowledge (questionnaire) [19]
Cardioprotective medication use (hospital records and self-report)
Diabetic control (HbA1C)

Self-reported physical activity will be validated in a one-fifth subset of the cohort at 12 months by using accelerometers. Accelerometry is now considered the preferred method of objectively measuring physical activity as it provides data that allows individual examination of ambulatory activity frequency, intensity and duration [23,24]. For this trial an Actigraph GT1M (formerly Computer Science and Applications monitor), the most widely accepted accelerometer in research, will be utilised [25]. The matchbox size accelerometer will be attached to a belt that the participants in both the intervention and control groups will be asked to wear for a period of seven consecutive days at one year and three years. The Active Australia survey [26] records information from the seven-day period immediately prior to the survey, and therefore will be completed at the end of the week in which the accelerometer is worn. Thus the accelerometry data and Active Australia will record the same seven-day period.

To evaluate the generalisability of the previously proven CHOICE study [21], process measures of the intervention will include: record of participant recruitment, withdrawal from the program, the context of the interventions and the resources used. Barriers to implementation will be documented. Each participant will also answer questionnaires, which will determine the dose and exposure to the elements of the program. Through this we will examine fidelity of the program to the intervention components.

### Sample size

Given the compelling evidence that lowering TC lowers cardiovascular events, our sample size is calculated based on change in TC. In the previous study with 70/group, we found a 25.5 (SD 1.0) mg/dL (0.66 mmol/L) greater reduction in TC at 12 months in the CHOICE than control group. To demonstrate a difference between CHOICE and CHOICE-*plus *groups, 138 per group in the RCT will give 80% power (2-tailed, P < 0.05) to detect a 0.35 SD effect (13.5 mg/dl (0.35 mmol/L) difference) in TC at 12 months or 3 years. To demonstrate a difference between the control and intervention groups at the single randomized site, 64 patients will be needed in the control group for 80% power. To allow for 20% loss to follow-up and a design effect of up to 1.15 (ICC 0.05) due to cluster sampling, a total of 400 patients will be recruited across the four sites.

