### Group allocation

Patients meeting the inclusion and exclusion criteria will be approached by the hospital CR coordinator or research assistant, during their inpatient stay where possible, or via letter or telephone soon after hospital discharge. Those who volunteer will have a baseline assessment and an initial face-to-face module selection and goal-setting session (approximately one hour in duration). This session will take place during the inpatient stay or in outpatient clinical consulting rooms, or, if necessary, at the participant's home, within one month of discharge. After baseline measurements are completed, at three sites, participants will be randomly allocated to one of the two groups (CHOICE or CHOICE-*plus*). At the remaining site participants will be randomly allocated to one of three groups (control, CHOICE or CHOICE-*plus*). Randomisation will be undertaken by an independent researcher (at the University of Sydney) with a computer-generated random allocation sequence and will be concealed from the health professional obtaining consent and conducting baseline assessment.

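### The recruitment total of 400 does not reconcile with 138 per CHOICE arm plus 64 controls under the plan's own loss and design-effect allowances

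*Protocol article*

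**What the plan says.** All the figures are in the Sample size section of the protocol article.

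- CHOICE versus CHOICE-plus: "138 per group in the RCT will give 80% power (2-tailed, P < 0.05) to detect a 0.35 SD effect".
- Control versus intervention at the single site: "64 patients will be needed in the control group for 80% power". No effect size is given for this comparison.
- Allowances: "To allow for 20% loss to follow-up and a design effect of up to 1.15 (ICC 0.05) due to cluster sampling".
- Result: "a total of 400 patients will be recruited across the four sites".

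The Group allocation section places the controls inside one of those four hospitals. Three sites randomise to two arms, and then: "At the remaining site participants will be randomly allocated to one of three groups". The Design section describes the same layout. The allocation ratio at the three-arm site is not stated, and nowhere does the text say that the controls come on top of the 400.

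**The concern.** The paragraph sets two requirements, names two allowances and gives one total. A reader takes that total to cover everyone: it is called a total, it spans all four sites, and it follows directly after the control requirement. On that reading it is too small for the numbers in the same paragraph.

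The comparison at stake is the one that tests whether longer reinforcement adds benefit. A null result is a real possibility there, and it will be read against the stated 80% power. If part of the 400 is used for controls, the CHOICE arms are smaller than the paragraph says. If it is not, the recruitment target is understated by roughly the size of the control group.

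**Working it through.** **Inputs (Sample size section).** 138 evaluable per CHOICE arm (276 in two arms); 64 controls; loss 20%; design effect (DE) up to 1.15; effect 0.35 SD; two-sided 5%; total 400. Recruited number = evaluable × DE / (1 − loss).

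**1. Reproducing the 400.** Two CHOICE arms only: 276 × 1.15 / 0.8 = 396.75, or about 400. Backwards: 400 × 0.8 / 1.15 = 278 effective patients, or 139 per arm. That meets the 138 and leaves nothing for controls.

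**2. All three groups.** Evaluable need: 138 + 138 + 64 = 340.

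- Both allowances on everyone: 340 × 1.15 / 0.8 = 488.75, about 489.
- DE on the CHOICE arms only, since the controls come from one site: 396.75 + 64 / 0.8 = 396.75 + 80 = 476.75, about 477.
- Loss only: 340 / 0.8 = 425.
- Near misses: DE only, 340 × 1.15 = 391; loss taken as a 20% increase with no DE, 340 × 1.2 = 408. Each drops an allowance that the sentence says is included.

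Against 400, the gap with both allowances is 77 to 89 patients.

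**3. How generous is 138?** A two-sample t-test at 0.35 SD needs about 129 per arm for 80% power; 138 gives 82.6%. With 129 per arm, the three groups with both allowances still need (258 + 64) × 1.15 / 0.8 = 463, or 258 × 1.15 / 0.8 + 80 = 451 with no DE on the controls.

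**4. Power for CHOICE versus CHOICE-plus if the controls are inside the 400.** The number of controls recruited is an assumption, because no ratio is stated. The three values are 64 (no inflation), 80 (64 / 0.8) and 92 (64 × 1.15 / 0.8). The remainder is split equally between the CHOICE arms.

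| Controls recruited | Recruited per CHOICE arm | After 20% loss | Effective at DE 1.15 | Power at DE 1.15 | Power, no DE |
|---|---|---|---|---|---|
| 64 | 168 | 134.4 | 116.9 | 75.9% | 81.6% |
| 80 | 160 | 128.0 | 111.3 | 73.9% | 79.7% |
| 92 | 154 | 123.2 | 107.1 | 72.2% | 78.1% |

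In the middle row at DE 1.15, the effect detectable with 80% power is 0.377 SD.

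**5. Power if the controls are additional.** 200 recruited per arm, 200 × 0.8 / 1.15 = 139 effective, power 82.9%.

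Power for the control comparison is not computed here, since neither its effect size nor the allocation at that site is stated.

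**The case against.** A reader might infer that the trial will miss its 80% power. The documents do not support that, for three reasons.

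- *The controls may be additional.* The 400 is reproduced by the two CHOICE arms alone, and the Design section describes CHOICE versus CHOICE-plus as running across all four sites with controls at only one. If that is what was meant, the main comparison keeps about 83%. This stands as a possible reading, but the sentence then mislabels its number as the total.
- *The design effect is a weak basis for a power figure.* It is given as an upper limit. Patients are randomised individually within sites, so a between-site design effect does not simply divide the sample for a within-site comparison. Also, 1.15 with an ICC of 0.05 implies a cluster size of 4, from 1 + (4 − 1) × 0.05. This stands: the 72–76% is a lower range, not an expected value. It does not rescue the total, because loss alone already needs 425 for the stated components.
- *138 is more than 0.35 SD requires.* With 129 per arm and no design effect, the three groups need (258 + 64) / 0.8 = 402.5, which is close to 400. This also stands, and it explains why power stays near 80% without the design effect. But the plan states 138 and says the design effect is covered.

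A reader might also infer that the evaluable split is 128, 128 and 64. That follows only if exactly 80 controls are recruited within the 400, and the document fixes no such allocation.

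**Conclusion.** The point holds as an inconsistency between the stated total and its stated components. With both allowances, the three groups need about 477 to 489, not 400; the 400 corresponds to the CHOICE arms alone. This part rests only on figures in the paragraph.

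The effect on power depends on which reading is right:

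- Controls inside the 400, the reading the text implies: about 72–76% at the full 1.15 and about 78–82% with no design effect, for 64 to 92 controls recruited and equal CHOICE arms.
- Controls additional: about 83%, with a true total of about 477.

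The loss of power is therefore moderate at worst and absent on one reading. On either reading the paragraph needs correcting.

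**What to change.** State whether 400 includes the control group. Then do one of the following:

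- **If it does:** keep 400. Replace the 138 with the evaluable number per arm under the allocation actually used, and give the power with and without the design effect. For example, if 80 controls are recruited, 128 per arm gives about 80% without and 74% with 1.15. These numbers illustrate the form and should not be copied unless that allocation is the real one.
- **If it does not:** label 400 as the two CHOICE arms and give the true total including controls, about 477 when the controls are inflated for loss only.

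The cost is one reworded paragraph. Under the first option no patients are added, and the stated power may become slightly less favourable. Under the second, the published recruitment target rises to what the components already require.

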### Statistical analysis

Primary analyses will be conducted by intention-to-treat using SPSS for Windows (Version 12.01) and will be presented as mean and standard error of the mean or proportions. Differences in outcome measures, between and within groups, will be compared using repeated measures ANOVAs for continuous variables and either χ^2 ^tests or Fishers exact tests, as appropriate, for proportions of categorical variables. Two tailed p values of < 0.05 will be considered significant. Number needed to treat will also be calculated to estimate the number of patients who need to receive the CHOICE intervention to lower each of the major risk factors (TC, LDL-cholesterol, BP, smoking cessation, physical activity and overweight) to below current national targets.

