**Figure 1 F1:**
[figure not shown]
**Design of the CHOICE study**. ACS: acute coronary syndrome. CHOICE: Choice of Health Options In prevention of Cardiovascular Events.

Blinded assessments will be conducted at baseline and 36 months during a face-to-face interview. At 12 months, assessments will be completed by the intervention nurse and to ensure validity, a sample of 20 patients will have their measurements repeated by an independent assessor, blinded to group allocation. At follow-up assessments, additional data will be collected, including details of any unplanned hospital admissions, medications and doses and details of visits to the family physician, cardiologist and attendance at any community program pertaining to their heart health. Ethical approval for this study has been granted by Sydney South West Area Health Services and will be sought from the University of Sydney Human Research Ethics Committees. Written and informed consent will be obtained from all study participants prior to commencement.

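### Within-group change in smoking and other proportions is assigned to χ² or Fisher's exact tests, which treat repeated measurements on the same patients as independent samples

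*Protocol article*

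**What the plan says.** Statistical analysis fixes the methods in one sentence, beginning "Differences in outcome measures, between and within groups, will be compared using repeated measures ANOVAs for continuous variables and either". Its subject is both between-group and within-group differences. Continuous variables get a repeated-measures method. The sentence closes by offering a choice of χ² "tests or Fishers exact tests, as appropriate, for proportions of categorical variables". Proportions therefore get those two tests only, and no paired test is named. The significance rule is "Two tailed p values of < 0.05 will be considered significant".

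Outcome measures makes smoking a primary outcome: "The primary outcomes are TC, systolic blood pressure (SBP), smoking rates and physical activity levels at 12 and 36 months". The Design section shows that the same patients are followed: "Blinded assessments will be conducted at baseline and 36 months during a face-to-face interview", with a further assessment at 12 months.

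The Sample size section powers total cholesterol (TC) only: "138 per group in the RCT will give 80% power (2-tailed, P < 0.05) to detect a 0.35 SD effect", and for the single-site comparison "64 patients will be needed in the control group for 80% power". The article gives no baseline smoking rate, no expected change, no within-patient correlation, and no power for any proportion or any within-group change.

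**The concern.** Pearson's χ² and Fisher's exact test compare proportions from independent samples. A within-group comparison of smoking at baseline and follow-up uses each patient twice. Its null hypothesis is that the two marginal proportions are equal in paired data. A patient's smoking status at one visit strongly predicts it at the next, so a standard error that ignores the pairing is too large. The test then falls below its nominal level and can miss a real fall in smoking.

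This is a rule that the article states, not a detail it leaves out, and the same sentence handles pairing correctly for continuous outcomes. At stake are within-group statements about a primary outcome, and about any other proportion followed over time, such as medication use or attainment of the dietary target. Under Group allocation, three of the four sites randomise only between the two CHOICE programs, so change from baseline is likely to be looked at there.

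**Working it through.** **The plan's own figure.** The only fully specified power figure is 138 per group for TC. The usual formula gives n = 2(1.960 + 0.842)²/0.35² = 129 per group (130 with the t distribution), and 138 gives about 82.8% power. The difference is on the safe side and does not bear on this point. No figure for proportions exists to reproduce, so 138 and 64 serve below only as plausible group sizes.

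**Inputs.** From the article: n = 138 or 64, two-sided 0.05. Assumed: smoking rates p₁ (baseline) and p₂ (follow-up), and within-patient correlation phi.

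**Formulas.** Proportion smoking at both visits: p₁₁ = p₁p₂ + phi·√[p₁(1−p₁)p₂(1−p₂)]. Quitters: p₁₀ = p₁ − p₁₁. New or resumed smokers: p₀₁ = p₂ − p₁₁.
- Standard error used by the unpaired χ²: √[2p̄(1−p̄)/n], where p̄ = (p₁ + p₂)/2.
- True standard error of the paired difference: √{[p₁₀ + p₀₁ − (p₁ − p₂)²]/n}.
- McNemar's null standard error: √[(p₁₀ + p₀₁)/n].

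**No change (p₁ = p₂).** The true standard error is √(1 − phi) times the one the χ² test uses. The real rejection rate is therefore 2[1 − Φ(1.96/√(1 − phi))], whatever the rate or n:
- phi 0.3: 1.96/0.837 = 2.34, so 1.9%.
- phi 0.5: 1.96/0.707 = 2.77, so 0.6%.
- phi 0.7: 1.96/0.548 = 3.58, so below 0.1%.

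**A fall from 30% to 20%, n = 138, phi 0.5.** p₁₁ = 0.06 + 0.5 × 0.1833 = 0.1517, so p₁₀ = 0.1483 and p₀₁ = 0.0483.
- Unpaired standard error: √(2 × 0.25 × 0.75/138) = 0.0521. Significance needs a difference of 0.1022.
- True standard error: √[(0.1967 − 0.01)/138] = 0.0368. Power of the unpaired test: Φ[(0.10 − 0.1022)/0.0368] = 48%.
- McNemar null standard error: √(0.1967/138) = 0.0378. Significance needs 0.0740. Power: Φ[(0.10 − 0.0740)/0.0368] = 76% by this approximation, and 79% by simulation.

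**Simulation** (at least 100,000 runs per row; Pearson χ² on the two visits as separate samples against asymptotic McNemar; percentage of runs rejecting):

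| Assumed change | n | phi | Unpaired χ² | McNemar |
|---|---|---|---|---|
| 30% to 30% | 138 | 0.3 | 1.9 | 5 |
| 30% to 30% | 138 | 0.5 | 0.6 | 5 |
| 30% to 30% | 138 | 0.7 | <0.1 | 5 |
| 30% to 20% | 138 | 0 | 48 | 48 |
| 30% to 20% | 138 | 0.3 | 48 | 63 |
| 30% to 20% | 138 | 0.5 | 48 | 79 |
| 30% to 20% | 138 | 0.65 | 46–47 | 92 |
| 40% to 20% | 138 | 0.3 | 98 | 99 |
| 40% to 20% | 138 | 0.5 | 99 | 100 |
| 30% to 25% | 138 | 0.7 | 3 | 39–40 |
| 30% to 20% | 64 | 0.5 | 18 | 43 |

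Exact McNemar is somewhat less powerful than the asymptotic test: for 30% to 20% with n = 138, 56% at phi 0.3 and 71% at phi 0.5. It still exceeds the unpaired test. Fisher's test was not simulated. It makes the same independence assumption, so it does not repair the problem.

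**The case against.** **The wording is condensed.** McNemar's statistic is itself referred to a χ² distribution, and a journal article may compress it into χ² tests used as appropriate. This is possible but strained. The phrase offers a choice between χ² and Fisher's exact test, the usual pair for independent samples, and Fisher's test cannot be read as paired. If McNemar's test was meant, naming it settles the matter.

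**The randomised question is untouched.** This stands. CHOICE against CHOICE-plus, and each against control at the one site, are between-arm comparisons, and at a single visit this pairing problem does not arise. The sample size rests on TC, a continuous outcome.

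**Replication does not hang on it.** This also stands. A reader might infer that replication at the three sites without a control group rests on a within-group smoking p-value. The article nowhere says so, and an uncontrolled before-after change following an acute coronary syndrome would be weak evidence of program effect under any test.

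**No false claims of benefit.** A reader might infer that the named tests would report change where there is none. That would need someone to cross-tabulate baseline against follow-up and read the association between visits as change. The article speaks of differences in proportions, so the natural reading is a comparison of two visits as two samples. On that reading, with positive correlation, the test errs towards caution.

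**Conclusion.** The point holds as a wrong method statement of limited reach. Within-group changes in proportions, including a primary outcome, are assigned to tests that assume independent samples. With positive within-patient correlation the test runs well below its nominal 5% (1.9% at phi 0.3, 0.6% at phi 0.5) and loses power.

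The direction of the level error follows from the pairing alone; the amount of power lost does not. A reader might take a loss of about half as the general figure. It appears only in some assumed scenarios, such as a 10-point fall with phi around 0.5 to 0.7. Elsewhere the loss runs from almost none (40% to 20%) to nearly all (30% to 25% at phi 0.7). The article supplies no smoking rates or correlation with which to narrow this range. The change is worth making because it is simple and concerns a primary outcome, but no randomised between-arm comparison at a single visit is put in doubt.

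**What to change.** In Statistical analysis, separate the two kinds of comparison:
- Keep χ² or Fisher's exact tests for between-group comparisons of proportions at one visit.
- For within-group change in binary outcomes (baseline to 12 months, baseline to 36 months), use McNemar's test, in its exact form when discordant pairs are few. Report the paired difference in proportions with its 95% confidence interval.
- Alternatively, fit one GEE or mixed logistic model with arm, visit and arm-by-visit terms, which gives both the within-arm changes and the between-arm contrasts.
- For ordered outcomes such as angina class, use a paired ordinal or marginal-homogeneity method, unless the outcome is dichotomised by a stated rule.

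The cost is a sentence or two of text, with no new data and no more patients. McNemar's test is a standard procedure in statistical packages. If the model is preferred, check first that the software version named in the article can fit it.

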CHD is a chronic condition, and changes to lifestyle and adherence to pharmacotherapy have to be life-long. Studies have tried to address this evidence-practice gap through education and counselling of risk factor targets and medications with success [15,16]. Using a simple, innovative patient-centred modular approach to secondary prevention in a randomised controlled trial (n = 208) [17,18], it was found that the Choice of Health Options In prevention of Cardiovascular Events (CHOICE) program was readily acceptable to ACS survivors who did not access standard CR. It was also found that the intervention group significantly reduced individual cardiovascular risk factors and overall risk, and had significantly better risk factor knowledge at both three and 12 month follow-up compared to baseline and compared to having conventional care with their usual general practitioner and/or cardiologist [19-21]. Therefore, it was demonstrated at a single hospital site that the evidence-practice gap could be reduced for up to 12 months.

The original CHOICE trial provided a successful secondary prevention option for patients not accessing CR at a single site but it is now imperative to determine if the findings are replicable at multiple sites, delivered by multiple health professionals and to examine the processes which influence the implementation of a successful trial into a "real-life" setting [22]. The aim of this study is to establish if the CHOICE program can be replicated at multiple hospitals over three years. We also aim to investigate whether 30 months of telephone support is more beneficial than three months.

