## Methods/design

### Design

This replication study, with a single site randomised control group, with three year follow up will be conducted at four tertiary referral hospitals in Sydney, Australia (figure 1) and is registered on the Australian and New Zealand Clinical Trials Registry (ACTRN12608000182392). Across all four sites patients not accessing standard CR will be randomly allocated to either a group participating in a three month CHOICE program or a 30 month CHOICE program (CHOICE-*plus*). At one site, patients not accessing CR will be allocated to one of three groups; the previously described intervention groups or a randomised control group participating in conventional care (figure 1), which will allow investigation of the effect of an additional nutrition module and a more tailored approach to depression.

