## Discussion

The findings of this replication study could have wide-ranging implications for the management of patients with CHD who are at highest risk of adverse events, namely survivors of an ACS. We anticipate this study will demonstrate that the large evidence-practice gap for the many ACS survivors not accessing CR can be narrowed by a brief, flexible and tailored modular intervention (CHOICE) to change behavior, reduce overall cardiac risk, and thereby reduce the likelihood of death, infarction, and recurrent symptoms. By demonstrating the generalisability of the previously proven CHOICE program, this approach, using existing personnel and community resources could easily be adopted state-wide at relatively low cost.

The ultimate goal for our patients is to maintain behavioural change and risk factor reduction in the long term within their local community. At the conclusion of this study we anticipate that we will be able to determine whether ongoing reinforcement is important to lower risk, and if this strategy can be implemented at multiple sites and consequently narrow the evidence-practice gap in the longer term.

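### Replication of CHOICE's effect can be tested against conventional care at only one of the four hospitals; at the other three, within-group tests could be significant with no programme effect

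*Protocol article*

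**What the plan says.** The Background states two aims. The first is "The aim of this study is to establish if the CHOICE program can be replicated at multiple hospitals over three years". The second is "We also aim to investigate whether 30 months of telephone support is more beneficial than three months".

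The Sample size section describes the earlier result as a "25.5 (SD 1.0) mg/dL (0.66 mmol/L) greater reduction in TC at 12 months in the CHOICE than control group". The finding to be replicated is therefore a between-group difference.

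Under Group allocation, "at three sites, participants will be randomly allocated to one of the two groups", namely CHOICE or CHOICE-plus. "At the remaining site participants will be randomly allocated to one of three groups", the third being conventional care. The Interventions section gives both active arms the same three-month programme; CHOICE-plus adds later reinforcement.

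The Design section says of the control group that it is something "which will allow investigation of the effect of an additional nutrition module and a more tailored approach to depression". The Sample size section sizes a control comparison at that one site, with 64 controls for 80% power.

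The Statistical analysis section states: "Differences in outcome measures, between and within groups, will be compared using repeated measures ANOVAs for continuous variables". Two-tailed p < 0.05 counts as significant. The Discussion looks ahead with "By demonstrating the generalisability of the previously proven CHOICE program".

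**The concern.** A result defined against conventional care can be reproduced only where conventional care is observed. At three sites every participant receives CHOICE in some form, so the randomised contrast there compares longer with shorter support. That answers the second aim and says nothing about whether CHOICE works at those hospitals. What remains within those sites is change from baseline.

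Baseline is taken during the admission or within one month of discharge (Group allocation). Cholesterol, blood pressure, activity and smoking can all move after an acute coronary syndrome through discharge treatment and recovery. A within-group test cannot separate that movement from a programme effect, and a site term or site-by-site tables would not help, because the comparator itself is absent. The first-named aim could then appear to be met at several hospitals when the programme had added nothing, and the Discussion links that aim to state-wide adoption.

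**Working it through.** **1. The plan's own figures.** A 0.35 SD effect is equated with 0.35 mmol/L, so the implied SD of TC is 0.35 / 0.35 = 1.0 mmol/L. For 0.35 SD at 80% power, two-sided 0.05, a two-sample t-test needs about 130 per group; the stated 138 gives about 83% power, a small conservative difference that does not bear on this point. The 64 controls are reproduced by assuming a 0.5 SD effect with equal arms (t-test: 64), an effect the article does not state. The total follows from 2 × 138 / 0.8 × 1.15 = 397, close to 400, a sum that does not include the controls.

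**2. CHOICE patients at the two-arm sites (assumed).**
- If the three-arm site takes 3 × 64 = 192 of the 400, then 400 − 192 = 208 remain. Split 1:1 this is 104 per arm, and after 20% loss 104 × 0.8 = 83.
- If the controls come on top of the 400, CHOICE has 200 in all. With 64 of them at the three-arm site, 200 − 64 = 136 remain, and 136 × 0.8 = 109, about 110.

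**3. Chance of a significant within-group fall with zero programme effect.** With an SD of 1.0 at each visit and baseline to follow-up correlation r, the SD of change is √(2(1 − r)): 1.18, 1.00 and 0.77 mmol/L for r = 0.3, 0.5 and 0.7. The power of a one-sample t-test on change (two-sided 0.05) for a background fall is then:

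| Background fall (mmol/L) | n = 83, r = 0.5 | n = 83, r = 0.3 to 0.7 | n = 110, r = 0.5 |
|---|---|---|---|
| 0.1 | 15% | 12% to 21% | 18% |
| 0.2 | 44% | 33% to 64% | 55% |
| 0.3 | 77% | 63% to 94% | 88% |

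At n = 83 and r = 0.5, a fall of 0.31 mmol/L gives 80%; that is 0.31 / 0.66 = 47% of the earlier effect. The fall itself, r and n are assumptions; the article gives none of them.

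**4. The controlled contrast already in the plan.** CHOICE v control at the three-arm site, SD 1.0, equal arms, true difference 0.66 mmol/L:
- 64 per arm recruited, 64 × 0.8 = 51 evaluable: power 91%; 95% CI half-width 1.96 × √(2/51) = 0.39 mmol/L.
- 64 per arm evaluable: power 96%; half-width 1.96 × √(2/64) = 0.35 mmol/L.

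A randomised test of the original effect with good power therefore exists, at one hospital.

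**The case against.** A reader might infer that the plan will report a significant within-group change as replication. No section says so. The analysis sentence is general, ties no p-value to the replication aim and sets no criterion for replication; a condensed article may leave such a criterion to the full protocol or analysis plan, so its absence is not held against the trial. That objection stands, and the point is confined to what within-group testing could suggest.

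The controlled comparison is also already sized and falls under the between-group analysis. That stands too, although the Design section gives the control group a different purpose, so its role in the replication aim is unclear.

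The multi-site aim is partly about implementation. The Outcome measures section names process measures (recruitment, withdrawal, context, resources, exposure and fidelity) as the means of evaluating generalisability, and the Discussion closes on whether the strategy can be implemented at several sites. On that reading, four sites without four control groups is a reasonable design. But process measures show delivery rather than effect, while the primary outcomes are risk factors and the Discussion also expects lower cardiac risk. The text supports both readings.

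Finally, 77% on its own would overstate the problem, since it needs an assumed background fall of 0.3 mmol/L; at 0.1 the chance is 15%. The direction of background change is not documented either.

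**Conclusion.** The point holds as a limit on inference. Three of four sites have no conventional-care comparator, so the effect of CHOICE against conventional care can be tested by randomisation at one site only. No analysis plan can supply the missing arm. Change from baseline elsewhere could be significant with no programme effect: 15%, 44% or 77% of the time for background falls of 0.1, 0.2 or 0.3 mmol/L, given SD 1.0 mmol/L, r = 0.5 and 83 evaluable CHOICE patients.

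Two stronger readings are not supported. One is that the trial cannot test CHOICE at all: the single-site contrast has about 91% to 96% power for 0.66 mmol/L under equal arms. The other is that its randomised comparisons are biased: CHOICE v CHOICE-plus is randomised at every site and is untouched. This is a should-fix.

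**What to change.** - **Statistical analysis:** name the randomised CHOICE minus control difference in TC at the three-arm site as the test of the programme's effect, reported with its 95% CI beside the earlier 0.66 mmol/L.
- **Statistical analysis:** do not use within-group p-values as evidence of effect. For the two-arm sites, report change from baseline with confidence intervals, labelled as uncontrolled, and set it beside CHOICE-arm change at the controlled site as a consistency check only.
- **Abstract, Background and Discussion:** state that replication of effect is tested at one site, and that delivery and generalisability across four sites rest on the process measures in the Outcome measures section.

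The cost is wording only, with no new patients or data. The downside is a narrower claim.
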